### Data analysis

The analysis will be performed with the intention to treat, and stratified for severity of prolapse. Patient characteristics will be summarized using descriptive statistics for continuous variables (mean ± standard deviation, minimum, maximum, and sample size) and frequency tables for categorical variables (numbers and percentages). Differences in group means were tested by Student’s *t* test, or Wilcoxon rank-sum test where data failed to follow a normal distribution after testing with the Kolmogorov-Smirnov test for normality. Differences in group proportions were tested using a chi-square test, or a Fisher’s exact test if data were sparse. Subgroup analysis based on body mass index (BMI) (< 24, ≥ 24), presence of concomitant surgical procedures, or prolapse stage (stage 2, stage 3, and stage 4) will be performed to identify the potential indication for each technique. Statistical analysis was performed using SPSS 20 for Windows (IBM Corp., Armonk, NY, USA) with *p* < 0.05 considered as statistically significant.

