**Methods:**

The trial is a randomized controlled trial. It compares LILS with LSC in women with stage 2 or higher uterine prolapse. The primary outcomes of this study are perioperative parameters, including surgical time, blood loss, intraoperative complications, and hospital stay as well as surgical anatomical results using the pelvic organ prolapse questionnaire (POP-Q) classification at 6 weeks, 6 months, 12 months, and annually till 5 years after surgery. Secondary outcomes are subjective improvement in urogenital symptoms and quality of life, postoperative complications, postoperative recovery, sexual functioning, and cost-effectiveness at each follow-up point. Validated questionnaires will be used and the data will be analyzed according to the intention-to-treat principle. Based on an objective success rate of 90%, a noninferiority margin of 15%, and a dropout of 20%, 107 patients are needed in each arm to prove the hypothesis with a 95% confidence interval.

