### Randomization

After signing an informed consent form, patients are randomized in a 1:1 ratio to either LILS or LSC centrally using a computerized random number generated at the moment of inclusion by a non-physician blinded to the women’s history and with no contact with the patients. Randomization will be stratified according to severity of prolapse (POP-Q stage 2, 3, or 4). The details of the series will be withheld from the investigators or to the participating gynecologists and all participants will receive unique study numbers. The subjects will be informed about the allocated operative procedure shortly after the randomization. Those who withdraw after randomization will be treated according to the preference of the gynecologist.

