## Statistical analysis

### Sample size and power considerations

The sample size for this trial was estimated based on the hypothesis that both interventions are equivalent in anatomical success rate within a 1-year follow-up. A review [13] including 12 publications [14–24] showed an objective success rate of 78% to 100% for LSC. Thus, the sample size was calculated based on objective success rates of 90% within 1 year. If a two-sided alpha level of 5% was applied, then 89 individuals per group would be required to achieve a power of 1-β = 80% for a noninferiority margin of 15%. The rate of loss to follow-up without recurrence of prolapse is expected to sum up to 20%. Finally, a total of 214 participants (107 for each group) will be needed. Anatomical success rate at each follow-up point assessed by a POP-Q-examination in both study groups will be considered as primary outcome. Surgical anatomical success rate is defined as less than stage 1 (all vaginal sites at least 1 cm above the hymen on Valsalva), as scored by the POP-Q system. Noninferiority of LILS to LSC will be concluded if the lower limit of the 95% confidence interval in anatomical success rates lies above the noninferiority margin of -15% [25].

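### Noninferiority is judged on intention to treat alone, with no check in women who received the allocated operation, although treatment after withdrawal is left to the gynecologist

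*Protocol article*

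**What the plan says.** The Data analysis section of the protocol article states: "The analysis will be performed with the intention to treat, and stratified for severity of prolapse". The abstract agrees: "the data will be analyzed according to the intention-to-treat principle". The article names no per-protocol or as-treated analysis.

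The section on sample size and power fixes the decision rule: LILS is noninferior if the lower 95% limit of the difference in anatomical success is above -15 points. The rule names no analysis set, so the general intention-to-treat statement governs it.

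The Randomization section says that women are told their allocated operation shortly after randomization, and then: "Those who withdraw after randomization will be treated according to the preference of the gynecologist". It does not say whether these women receive the other trial operation, or whether they are followed and counted in their randomized arm.

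On attrition, the sample-size section says: "The rate of loss to follow-up without recurrence of prolapse is expected to sum up to 20" percent. That figure is used only to enlarge the sample.

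**The concern.** In a superiority trial, intention to treat is usually the cautious choice, because mixing of treatments makes a difference harder to show. In a noninferiority trial the same mixing moves the observed difference towards zero, and that is the direction that produces the claim.

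The article leaves a route for such mixing. Allocation is known before surgery, treatment after withdrawal is left to preference, and the surgeons are experienced in both operations. The Discussion adds that the investigators regard LILS as suitable where the promontory is hard to reach.

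At stake is a claim that LILS is noninferior when it is in truth 15 points worse. The Discussion says that once noninferiority is found, the secondary outcomes will guide the choice between the operations, so a false claim would carry straight into that choice.

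**Working it through.** **Inputs from the article**
- Success rate: "the sample size was calculated based on objective success rates of 90% within 1 year", taken for both arms.
- Error level: "If a two-sided alpha level of 5% was applied", that is 2.5% one-sided for noninferiority.
- Power and margin: "to achieve a power of 1-β = 80% for a noninferiority margin of 15" percentage points.
- Size: "then 89 individuals per group would be required", raised to 107 per group for 20% loss. After 20% loss, 107 × 0.8 = 85.6, about 86 per group.

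**Assumed, not in the article**
- The share c of analysed women who receive the other operation.
- True rates exactly at the margin: 90% (LSC) and 75% (LILS). Any claim of noninferiority is then false.

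**The plan's own figure.** The usual formula gives n = 2 × 0.90 × 0.10 × (1.96 + 0.8416)² / 0.15² = 62.8, so 63 per group, not 89. A rate of 85% in both arms would give 2 × 0.85 × 0.15 × 7.849 / 0.0225 = 88.95, so 89, but 85% is not the stated rate. For this point it matters only that 89 is on the large side, so power is not short on the stated inputs. The enlarged size is 89 × 1.2 = 106.8, so 107.

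**Effect of crossing, normal approximation, 86 per group.** If a share c of LILS women receive LSC, the expected LILS rate is pA = 0.90 - 0.15 × (1 - c) and the expected difference is d = 0.15 × (1 - c). The standard error is SE = √[(0.09 + pA(1 - pA)) / 86]. The false-claim rate is 1 - Φ(1.96 - (0.15 - d)/SE).
- c = 0: 2.5%.
- c = 0.10: pA = 0.765, d = 0.135, SE = 0.0560; 1.96 - 0.015/0.0560 = 1.692; rate 4.5%.
- c = 0.20: pA = 0.78, d = 0.12, SE = 0.0552; 1.96 - 0.030/0.0552 = 1.416; rate 7.8%.

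The switch that the Discussion makes more plausible runs the other way, from LSC to LILS. With 10% of LSC women receiving LILS, the expected LSC rate is 0.885, SE = 0.0580, and the rate is 4.4%. The direction of the switch hardly matters.

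**Exact check.** Binomial enumeration of the stated rule with a Wald 95% interval, 107 per group:

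| Share crossing (assumed) | LILS women receive LSC | Both directions |
|---|---|---|
| 0% | 2.8% | 2.8% |
| 5% | 3.9% | 5.3% |
| 10% | 5.3% | 9.1% |
| 20% | 9.6% | 22.3% |

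With 89 per group, one-way crossing of 10% and 20% gives 5.0% and 8.6%.

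**Effect of 20% loss, same true rates, loss unrelated to outcome, exact**
- Complete cases, 86 per group: 3.0%, practically the 2.8% seen without loss.
- All lost women counted as failures (72% v 60%, 107 per group): 6.8%.
- All lost women counted as successes (92% v 80%, 107 per group): 10.3%.

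The last two rows need a single fill-in value for both arms, which shrinks the true 15 points to 12. The article states no such rule.

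**Power with a per-protocol set.** Power = Φ(0.15/√(0.18/n) - 1.96) at 90% in both arms:
- 86 per group: 90.6%.
- A further 10% excluded (107 × 0.8 × 0.9, about 77): 87.3%.
- A further 20% excluded (107 × 0.8 × 0.8, about 68): 83.0%.
- 63 per group: 80%.

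These are figures for one set. The chance that both sets pass is somewhat lower.

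**The case against.** The strongest reply is that naming intention to treat is no error. It preserves the randomized comparison, it does not rule out a supportive per-protocol analysis, and a condensed article may leave further sets to an analysis plan that is not shown. Part of this stands: methods for missing data and their sensitivity checks may properly sit in such a plan, and their absence here is not a fault. What remains is that the article itself fixes the decision rule and the only set behind it, with no consistency condition. A further set added elsewhere would have no part in the claim as worded.

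Second, a reader might infer from the Randomization section that withdrawn women cross to the other operation. The text does not say so. It describes women who withdraw, and it leaves open what treatment they get and whether follow-up continues. Dilution needs both: the other operation, and a result counted in the randomized arm. Women who leave follow-up belong to the missing data instead, and should not be counted under both headings. If the preferred treatment is neither trial operation, the direction of the effect depends on its success rate. This objection stands, and it makes the concern conditional.

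Third, a reader might infer that the expected 20% loss also pulls the arms together. The documents do not support that. Loss can leave the difference unbiased, shrink it or widen it, depending on its relation to outcome and on a rule that the article does not give.

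Fourth, a per-protocol set drops women after randomization and can be biased in either direction. That is true, and it is a reason to place it beside intention to treat and not in its stead.

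**Conclusion.** The concern holds in a conditional form. The noninferiority claim depends on one analysis set, that set is open to dilution if women who depart from allocation are followed and analysed as randomized, and nothing in the stated rule asks whether the conclusion survives in women who had the allocated operation.

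At true rates on the margin, one-way crossing of 10% roughly doubles the nominal error, and 20% brings it to three or four times nominal. These sizes rest on assumed crossing shares. If crossing is rare, or if withdrawn women leave follow-up, dilution by crossing is small or absent. This is a worthwhile improvement at low cost, not a flaw that invalidates the design.

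**What to change.** Keep intention to treat. Add a per-protocol analysis of 12-month anatomical success, the time point on which the sample size is based, in eligible women who received the allocated operation. Use the same -15 point margin, and word the decision rule so that noninferiority is claimed only if the lower 95% limit is above -15 points in both sets. If the two disagree, noninferiority is not claimed.

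This takes a few lines of text and one more run of the same analysis, provided that the operation actually received is recorded for each woman. The 214 planned women suffice on the stated inputs. The costs are slightly less power, because both sets must pass and the second is smaller, and possible selection bias in the per-protocol set, which should be acknowledged when the results are read.

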### Primary and secondary outcomes

The primary outcomes of this study included perioperative parameters such as surgical time, blood loss, intraoperative complications, hospital stay, and anatomical success rate using the POP-Q classification at 6 weeks, 6 months, 12 months, and annually till 5 years after surgery. The POP-Q system has been developed by the International Continence Society and is a reliable and reproducible method for assessing organ descent [10]. The lowest level of organ descent during Valsalva is measured relative to its distance from the hymen: points above the hymen are negative and those below are positive; vaginal support at the level of hymen is represented as ‘0 cm’. The anatomical success rate is defined as less than stage 1 (all vaginal sites at least 1 cm above the hymen on Valsalva), as scored by the POP-Q system. Secondary outcomes of this study include subjective outcome and improvement in general and disease-specific quality of life, short- and long-term complications, postoperative recovery, sexual functioning, and cost-effectiveness after LILS or LSC at each follow-up point.

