### Data collection

All patients will undergo routine gynecological examination, which is part of the standard procedure before surgery. This examination includes pelvic ultrasound to exclude uterine or ovarian disease, routine cervical screening, and vaginal inspection in a 45° semi-upright position for staging uterovaginal prolapse by POP-Q examination on maximum Valsalva effort in the lithotomy position. Urodynamic testing will also be performed in patients with urinary incontinence.

Demographics, medical, and obstetric history, previous pelvic floor and gynecological surgery were collected using standardized questionnaires. The anatomical success rate as scored by the POP-Q system and subjective satisfaction rate according to the Patient Global Impression of Improvement Scale (PGI-I) scale that integrates bladder, bowel, prolapse, sexual function domain, severity, bothersomeness, and condition-specific quality of life were recorded [11]. Other questionnaires included symptom severity, quality of life, and sexual activity in accordance with the Pelvic Floor Distress Inventory (PFDI-20), Pelvic Floor Impact Questionnaire (PFIQ-7) and the Pelvic Organ Prolapse/Urinary Incontinence Sexual Questionnaire (PISQ-12) scores at baseline and postoperation at 12 months. The PFDI-20 and PFIQ-7 questionnaires consist of three subscales each. PFDI-20 reflects the different perspectives of bulging symptoms (Pelvic Organ Prolapse Distress Inventory-6, POPDI-6), bowel problems (Colorectal-Anal Distress Inventory-8, CRADI-8), and urinary symptoms (UDI-6: Urinary Distress Inventory-6, UDI-6). PFIQ-7 describes the different impacts on a woman’s social life related to urinary tract (Urinary Impact Questionnaire-7, UIQ-7), bowel or rectal (Colorectal-Anal Impact Qestionnaire-7, CRAIQ-7), and vaginal or pelvic symptoms (Pelvic Organ Prolapse Impact Questionnaire-7, POPIQ-7). PISQ-12 describes sexual function in relation to prolapse or urinary incontinence. High PFDI-20 and PFIQ-7 indicate impaired function, and a high PISQ-12 score indicates good sexual function [12].

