Intraoperatively, patients are assessed for operative time, blood loss, and complications. The impact of bleeding is also assessed by the measurement of hemoglobin levels 24 h after surgery. During hospitalization and in the first 6 weeks after surgery, the patients are asked to keep a diary, which contains the following items: postoperative pain measured by the Visual Analogue Score (VAS), pain medication intake and the Recovery Index-10 (RI-10) recovery questionnaire. The RI-10 recovery questionnaire is a validated quality-of-life questionnaire measuring subjective postoperative recovery.

Postoperatively, patients will visit the hospital at 6 weeks (routine postoperative consultation), 6 months, 12 months, and yearly thereafter. The total duration of the follow-up period is 5 years. Each check-up point includes answering a standardized written questionnaire regarding symptom severity, quality of life, and sexual activity (similar to the questionnaires at baseline) and a clinical examination (including POP-Q). The long-term complications in both groups are recorded.

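### The plan names no baseline-adjusted analysis for the questionnaire scores, leaves open whether follow-up or change scores are tested, and gives two schedules for collecting them

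*Protocol article*

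**What the plan says.** **Analysis.** In the protocol article, Data analysis gives one rule for continuous outcomes: "Differences in group means were tested by Student’s *t* test, or Wilcoxon rank-sum test", the latter where the data are not normal as judged by a Kolmogorov-Smirnov test. The section opens with a general statement: "The analysis will be performed with the intention to treat, and stratified for severity of prolapse". It does not mention PFDI-20, PFIQ-7 or PISQ-12, and it does not say whether the score at a visit or the change from baseline is compared. Under Primary and secondary outcomes, the quality-of-life outcome is worded as an improvement.

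**Timing.** The second paragraph of Data collection names the three instruments and gives their "scores at baseline and postoperation at 12 months". Later in the same section, "patients will visit the hospital at 6 weeks (routine postoperative consultation), 6 months, 12 months, and yearly thereafter", up to 5 years, and "Each check-up point includes answering a standardized written questionnaire regarding symptom severity, quality of life, and sexual activity", described as similar to the baseline questionnaires. Primary and secondary outcomes ends its list of secondary outcomes with "sexual functioning, and cost-effectiveness after LILS or LSC at each follow-up point". The abstract uses the same timing.

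**Use.** The Discussion says that, if noninferiority is shown, the comparison of secondary outcomes will be essential in selecting the preferred operation. The Hypothesis section raises the possibility that LILS improves sexual functioning more than LSC.

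**The concern.** There are two separate problems with the same scores.

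First, a baseline score is usually the best single predictor of a later score on the same questionnaire. The trial pays to collect it, but the only tests named cannot take it as a covariate, nor, as named, the promised stratification by stage. The normality pre-test adds a further difficulty: the data choose the test, so one score or visit could be compared by means and another by ranks.

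Second, the document gives two collection schedules. In a multicentre trial, centres could follow different ones, and a questionnaire not completed at a visit cannot be filled in later.

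Both matter more than is usual for secondary outcomes, because the Discussion gives these outcomes a deciding role once noninferiority is shown.

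**Working it through.** **Precision.** The documents give no sample size, standard deviation, effect size or correlation for any questionnaire score, so there is no figure of the plan's own to reproduce.

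Inputs:
- From Sample size and power considerations: 107 per arm and 20% loss, so 107 × 0.8 = 85.6, taken as n = 86 per arm; two-sided 5% level. The 80% power used there is for anatomical success and is borrowed here for illustration.
- Assumed: baseline/follow-up correlation r = 0.3, 0.5 or 0.6, and equal variance σ² at both times.

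Variance of the estimated difference between arms:
- t test on follow-up scores: 2σ²/n
- t test on change scores: 2(1 − r) × 2σ²/n
- ANCOVA with baseline score: (1 − r²) × 2σ²/n

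The ratio of ANCOVA to the follow-up-score test is therefore 1 − r². Its ratio to the change-score test is (1 − r²)/[2(1 − r)] = (1 + r)/2. The reciprocal of each ratio gives the number of patients the simpler test would need relative to ANCOVA.

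| r | 1 − r² | Variance cut vs follow-up test | Patient equivalent | (1 + r)/2 | Variance cut vs change test | Patient equivalent |
|---|---|---|---|---|---|---|
| 0.3 | 0.91 | 9% | 1/0.91 = 1.10 | 0.65 | 35% | 1/0.65 = 1.54 |
| 0.5 | 0.75 | 25% | 1/0.75 = 1.33 | 0.75 | 25% | 1/0.75 = 1.33 |
| 0.6 | 0.64 | 36% | 1/0.64 = 1.56 | 0.80 | 20% | 1/0.80 = 1.25 |

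The smallest difference detectable with 80% power at 86 per arm, in SD units, is (1.960 + 0.842) × √(2/86) = 0.427 for the follow-up-score test. Multiplying by √(1 − r²) for ANCOVA gives 0.408, 0.370 and 0.342 at r = 0.3, 0.5 and 0.6. Multiplying by √[2(1 − r)] for change scores gives 0.506, 0.427 and 0.382. ANCOVA is the most precise of the three in every row. Any further gain from the stage term is not counted.

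**Timing.** The follow-up visits are 6 weeks, 6 months, 12 months, and 2, 3, 4 and 5 years: 7 in all. The sentence naming the instruments gives 1 postoperative measurement (12 months). The check-up sentence and the secondary-outcome definition give 7. If the former governed, 7 − 1 = 6 visits would have no PFDI-20, PFIQ-7 or PISQ-12 scores.

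**The case against.** The strongest case on the other side has four parts.

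- **The text may allow use of the baseline and the stratum.** A reader might infer that raw follow-up scores are tested with the baseline ignored and the stage stratum unused. The document does not support that. It never says which quantity is tested, improvement can mean change from baseline, and stratification by severity is stated. What stands is that the choice is left open, that no named method adjusts for baseline, and that the named tests do not carry the stratification. ANCOVA is more precise under either reading.
- **The named tests are valid.** A reader might infer that chance baseline imbalance biases the comparison. It does not: under randomization the unadjusted comparison is unbiased on average, and its standard error already allows for chance imbalance. The loss is of efficiency.
- **This detail belongs in an analysis plan.** Model form for secondary scores is often left to one, and silence here would be no finding. But the article is not silent: it names the tests, and a separate plan would have to override them.
- **The timing conflict may be one loose sentence.** The 12-month sentence does not say that this is the only postoperative measurement. The abstract, the Study design section, the secondary-outcome definition and the check-up sentence all point to questionnaires at follow-up visits generally, and the schedule figure, which is not available here, may settle it. A reader might infer that 6 of 7 comparisons cannot be made; that is so only if the 12-month sentence is followed. The two statements still disagree as written.

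It is also true that some secondary outcomes, such as postoperative complications and recovery, have no baseline score, so the precision point does not reach them.

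**Conclusion.** The point holds as a recommended improvement to the analysis together with a contradiction that needs resolving. The analysis part costs precision: at assumed correlations from 0.3 to 0.6, the named t test needs about 10% to 56% more patients than ANCOVA if follow-up scores are compared, and about 54% down to 25% more if change scores are. At 0.5 the figure is 33% on both readings. These sizes rest on the assumed correlation and equal variances, and they describe the t test; the Wilcoxon alternative was not quantified.

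The timing contradiction needs no assumption to establish. Its consequence, no scores at 6 of 7 visits, depends on which statement a centre follows. Neither part affects the primary anatomical comparison.

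**What to change.** 1. In Data analysis, state that each questionnaire score is analysed by ANCOVA, with the follow-up score regressed on arm, baseline score and POP-Q stage stratum, or by a mixed model over visits with the same terms. Report the adjusted difference with its 95% confidence interval, and drop the Kolmogorov-Smirnov pre-test for these scores. This settles which quantity is analysed and gives effect to the promised stratification.
2. Reconcile the 12-month sentence in Data collection with the check-up sentence in the same section, with Primary and secondary outcomes and with the abstract, so that one questionnaire schedule applies at all centres.

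The cost is slightly more analysis work and a few sentences of text. No extra patients are needed, and no extra visits, because the check-up sentence already schedules questionnaires at each one. The fix has a limit: the trial began in March 2016, so any scores already missed at a centre that followed the 12-month sentence cannot be recovered, and the report should say how many are missing at each visit.

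### Long-term complications are followed for 5 years, but the only comparison named for a yes/no outcome is chi-square or Fisher on raw proportions, which ignores time at risk

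*Protocol article*

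**What the plan says.** All references are to the protocol article.

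- **Primary and secondary outcomes** lists among the secondary outcomes "short- and long-term complications, postoperative recovery, sexual functioning, and cost-effectiveness after LILS or LSC at each follow-up point".
- **Data collection** schedules visits at 6 weeks, 6 months, 12 months and then yearly: "The total duration of the follow-up period is 5 years". That makes seven visits. It adds: "The long-term complications in both groups are recorded".
- **Sample size and power considerations** gives the only loss figure: "The rate of loss to follow-up without recurrence of prolapse is expected to sum up to 20" per cent. It stands in a calculation resting on the two operations being "equivalent in anatomical success rate within a 1-year follow-up". No 5-year loss, no loss by arm and no complication risk is given.
- **Data analysis** sets the analysis principle: "The analysis will be performed with the intention to treat, and stratified for severity of prolapse". For yes/no outcomes it names one approach: "Differences in group proportions were tested using a chi-square test", with Fisher's exact test as the alternative for sparse data. The rule is general. It neither mentions nor exempts long-term complications, and it states no denominator.
- **Discussion** says that, if noninferiority is found, the secondary outcomes will be essential for choosing between the techniques.

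**The concern.** Late complications accrue over years, and some women will leave before 5 years. A raw proportion treats a woman seen for 6 weeks and a woman seen for 5 years alike. If all randomised women stay in the denominator, which is the natural reading of intention to treat, those who leave early count as free of complications for time in which nobody observed them. The reported 5-year rate is then too low. If the denominator is restricted instead, the result depends on who is kept.

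Safety of a new mesh suspension is part of the trial's stated question, and the secondary outcomes are to guide the choice of technique. A 5-year complication rate that is wrong by a tenth or more of its value would enter that choice directly.

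**Working it through.** The article states no figure for complications, so there is none of its own to reproduce. The check asks what a raw proportion would show for a known true risk.

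**Inputs**
- From the article: 5 years of follow-up; 20% loss; 107 women per arm (taken as printed, for scale only).
- Assumed: a true 5-year risk R of 10%, with 5% and 20% as the range; constant event hazard; loss unrelated to complications; the timing of loss.

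**Formula.** The event hazard is λ = −ln(1 − R)/5. For R = 10%, λ = 0.02107 per year. If a fraction L is lost within a year, the loss hazard in that year is μ = −ln(1 − L). With all randomised women as denominator, a period of length t that starts with a fraction S still observed and event-free adds

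S × λ/(λ + μ) × [1 − exp(−(λ + μ)t)]

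to the raw proportion.

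**Case A: 20% is the whole 5-year loss, spread evenly.** μ = −ln(0.8)/5 = 0.04463. Raw proportion = 0.02107/0.06570 × (1 − 0.9 × 0.8) = 0.3207 × 0.28 = 0.0898, or 9.0%. This is about 10% too low in relative terms.

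**Case B: 20% lost in year 1, none later.**
- Year 1: μ = 0.2231. Contribution = 0.02107/0.24422 × (1 − 0.8 × 0.97915) = 0.08628 × 0.21668 = 0.0187.
- Years 2 to 5: 0.8 × 0.97915 = 0.7833 remain. Contribution = 0.7833 × (1 − exp(−4 × 0.02107)) = 0.7833 × 0.0808 = 0.0633.
- Total 0.0820, or 8.2%. This is 18% too low.

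**Case C: 20% lost in year 1, then an assumed 3%, 5% or 10% per year.** Raw proportions are 7.8%, 7.6% and 7.1%, or 22% to 30% too low.

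**Range over the assumed risk**

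| True 5-year risk | Case A | Case B |
|---|---|---|
| 5% | 4.5% | 4.1% |
| 10% | 9.0% | 8.2% |
| 20% | 18.0% | 16.4% |

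**Other denominators, true risk 10%**
- Women attending at 5 years, counting any past complication, with loss the same before and after an event: (0.10 × retention)/retention = 10%. There is no bias.
- Women with an event plus women who complete 5 years event-free, Case A: 0.0898/(0.0898 + 0.9 × 0.8) = 11.1%. The bias is upward.

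**Between arms, no true difference, all randomised as denominator**
- Equal loss: the gap is 0.
- Assumed 10% v 30% lost over 5 years: 9.5% v 8.4%, a gap of 1.1 points. At 107 per arm the two-sided rejection rate is 5.9% instead of 5%. At true risks of 5% and 20% the gaps are 0.5 and 2.1 points, with rejection rates of 5.4% and 6.8%.
- A more extreme assumption, 15% then 3% per year v 25% then 10% per year (75% v 49% retained): 8.3% v 6.7%. That is about 8.8 v 7.1 women, a gap of 0.44 standard errors.

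**The case against.** **This is detail for an analysis plan.** The document is a journal article, and neither the full protocol nor an analysis plan is shown. Denominators and handling of loss are commonly settled there, and the sentence on proportions is generic. This stands for the unstated denominator, which alone would not be a finding. It does not remove the point: the article states a method for yes/no outcomes, the method covers late complications by default, and it does not suit an outcome that accrues over 5 years.

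**The direction of bias is not fixed.** This stands. A reader might infer that complication rates will certainly be understated. That follows only if lost women remain in the denominator as event-free.

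**Heavy 5-year loss is not in the text.** This stands. A reader might infer it from the 20% figure, but 20% is the only loss given, and it sits in a 1-year calculation. The continuing loss in Case C is assumed.

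**The arm that loses more women would look safer only if loss differs.** This stands. Women are told which operation they are to have, so unequal loss is possible, but the article predicts none. Even with the unequal losses assumed above, the effect on the test is small.

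**Censoring does not cure informative dropout.** This stands too. If women leave because of a complication, Kaplan-Meier and log-rank estimates are also biased. Events found at yearly visits are dated only approximately, and a stratified hazard ratio may be unstable with few events.

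**The noninferiority decision is untouched.** This is correct. That decision rests on anatomical success.

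**Conclusion.** The point holds in a limited form. The stated comparison of raw proportions is a poor choice for complications collected over 5 years because it ignores time at risk. With all randomised women as denominator, loss unrelated to complications and a constant hazard, an assumed 10% risk reads as 9.0% or 8.2% when total loss is 20%, depending on when it occurs. These sizes rest on an assumed complication risk and on the assumed timing of loss.

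The documents do not support a claim that rates will necessarily be too low, or that one arm will look safer. The harm lies mainly in the reported absolute rates, not in the test between arms. It deserves correction because a better method is cheap and the outcome is meant to inform the choice of technique.

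**What to change.** In Data analysis, add a rule for long-term complications:

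- Analyse them as time from surgery to first event, censored at last contact.
- Report cumulative incidence with 95% confidence intervals by arm at 1 and 5 years.
- Compare arms with a log-rank test stratified by POP-Q stage, matching the randomisation strata. Give a hazard ratio only if there are enough events.
- Report loss to follow-up by arm and over time beside these results, because the method still assumes that loss is non-informative.
- Keep chi-square or Fisher for intraoperative and in-hospital complications, where follow-up should be essentially complete.

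The cost is a change of wording and the use of event and last-contact dates. The visits are already scheduled, so no extra visits or patients are needed. Complications found only at a visit would be dated to that visit, an approximation that should be stated.
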